### Objectives {7}

The purpose of this study is to compare the efficacy and safety of nalbuphine hydrochloride injection and morphine hydrochloride injection for perioperative analgesia in tumor ablation, evaluate clinically applicable nalbuphine and morphine in analgesic regimen for perioperative ablation, and provide an important reference for the development of clinical practice guidelines.

### Trial design {8}

This study is a superiority trial. We designed it by a multicenter, single-blind, randomized, parallel, positive-controlled clinical study to observe the efficacy and safety of nalbuphine hydrochloride injection and morphine hydrochloride injection for perioperative analgesia in tumor ablation. With such a study design, we hope to find a more effective and safe method of analgesia in the perioperative period for tumor ablation.

## Methods: participants, interventions, and outcomes

### Study setting {9}

The setting of this study is the interventional ward and interventional catheterization operating room of the hospital.

### Eligibility criteria {10}

Patients undergoing tumor ablation procedures are included.

Participants who meet the following inclusion criteria are eligible for this study:Patients who are diagnosed by clinicians and require tumor ablation surgery;Patients who provide written informed consent; andPatients aged 18–80 years.

The exclusion criteria are as follows:Allergy to contrast agents, test drugs, or other ingredients in the drug formulation;History of drug abuse, chronic pain, and mental illness;Use of monoamine oxidase inhibitors within 14 days before randomization;Pregnancy, lactation, and intolerance of surgery for other reasons;Difficulty correctly expressing needs or preferences;Poor compliance, inability to complete the trial according to the study protocol;Participation in other drug trials within 30 days before inclusion; andNot eligible to participate in this trial based on investigator opinion.

### Who will take informed consent? {26a}

Researchers will obtain informed consent or assent from potential trial participants or authorized surrogates. Informed consent was given verbally and in writing, dated and signed by the subject.

### Additional consent provisions for collection and use of participant data and biological specimens {26b}

Not applicable. We have described the terms of collection and use of participant data and biospecimens in the informed consent.

## Interventions

### Explanation for the choice of comparators {6b}

Opioids are the drugs of choice for the clinical treatment of pain, and morphine, as a classical opioid, is widely used in clinical practice.

### Intervention description {11a}

#### Intervention group

For the intervention group, nalbuphine 80 mg + 0.9% normal saline (72 ml) is pre-set in the PCA pump, and the pump is connected 15 min before ablation. Surgery is performed immediately under electrocardiogram (ECG) monitoring, with an initial dose of 0.15 ml/kg, a background dose of 0.5 ml/h, a compression dose of 2 ml, and a lockout time of 15 min. If the Numeric Rating Scale (NRS) score is ≥ 4 points, the drug is administered by compression. Pain intensity, incidence of adverse reactions (nausea and vomiting, dizziness, pruritus, constipation, hypoxemia, and urinary retention), satisfaction with analgesia, duration of surgery, postoperative hospital stay, average daily dose, uninterrupted completion rate of the surgery without complaints of pain, quality of life assessment, and vital signs are evaluated every 1 min and 5 min after ablation at the end of surgery, and 2 h, 6 h, 12 h, 24 h, and 48 h after surgery.

#### Control group

For the control group, morphine 80 mg + 0.9% normal saline (72 ml) is added in the PCA pump, which is connected 15 min before ablation. Surgery is performed immediately under ECG monitoring. The initial dose is 0.15 ml/kg, background dose is 0.5 ml/h, compression dose is 2 ml, and lockout time is 15 min. If the NRS is ≥ 4 points, the drug is administered by compression. Pain intensity and the incidence of adverse reactions (nausea and vomiting, dizziness, pruritus, constipation, hypoxemia, and urinary retention) were evaluated every 1 min and 5 min after ablation at the end of the surgery, and 2 h, 6 h, 12 h, 24 h, and 48 h after surgery. Satisfaction with analgesia, duration of surgery, postoperative hospital stay, average daily dose, uninterrupted completion rate of surgery without complaints of pain, quality of life assessment, and vital signs are also assessed.

### Criteria for discontinuing or modifying allocated interventions {11b}

During the study, the study can be terminated early/closed due to the following reasons: (1) Serious adverse events related to the test drug occurred during the study; (2) The effect of the drug was found to be too poor in the test, and there was no need to continue the study; (3) Major mistakes in the clinical trial protocol were found in the trial, and it was difficult to evaluate the drug effect; (4) The drug regulatory authority or the ethics committee requested to terminate the approved research.

An individual participant’s disenrollment criteria are as follows: (1) inability to complete the observation due to adverse events, (2) withdrawal invited by the investigator (poor compliance, serious adverse events), and (3) combination of prohibited drugs during the study period that prevented satisfaction and effectiveness evaluation.

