### Relevant concomitant care permitted or prohibited during the trial {11d}

During the study period,in addition to the test drug, other analgesic drugs (such as non-steroidal analgesics, antidepressants, etc.) shall not be newly added during the test period, but other drugs that do not affect the efficacy of opioids can be used.

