### Data management {19}

An electronic data capture system is used for data collection in this study. According to the GCP requirements for clinical trials in China, the data shall be maintained for 5 years after the termination of the clinical trial.The full analysis set (FAS) of the analysis dataset includes all subjects who were randomized, received the study drug, and had at least one efficacy evaluation data after medication. In case of missing data of the primary efficacy endpoint, the last observation carried forward is applied according to the intention-to-treat principle. The missing values for the comparability analysis and secondary efficacy measures are not carried forward and were based on the analysis dataset obtained in the FAS.Per protocol set (PPS) is a dataset generated from subjects who are fully compliant with the trial protocol; compliance includes receiving treatment, availability of the primary endpoint measures, and no major trial protocol violations. The per-protocol analysis is used mainly for the primary efficacy measures.Safety set (SS) refers to all subjects who are randomized, received the study drug, and have at least one post-baseline safety assessment.

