### Methods in analysis to handle protocol non-adherence and any statistical methods to handle missing data {20c}

Not applicable. Non-compliance with the protocol and missing data, we plan not to use as part of the statistical analysis.

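### The article gives two incompatible rules for disenrolled patients in the primary analysis, so whether they are dropped or can be scored as successes is undetermined, and the per-protocol set is no independent check

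*Protocol article*

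**What the plan says.** All sections are in the protocol article.

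- **Disenrolment, {11b}.** Three grounds: "inability to complete the observation due to adverse events"; withdrawal at the investigator's invitation, for poor compliance or serious adverse events; and "combination of prohibited drugs during the study period that prevented satisfaction and effectiveness evaluation". The section does not say whether readings continue, or what happens to data already collected.
- **Concomitant care, {11d}.** Other analgesics "shall not be newly added during the test period".
- **FAS, {19}.** It "includes all subjects who were randomized, received the study drug, and had at least one efficacy evaluation data after medication". Statistical methods {20a} repeats this population for the outcome analysis.
- **Missing primary endpoint, {19}.** "In case of missing data of the primary efficacy endpoint, the last observation carried forward is applied according to the intention-to-treat principle".
- **Non-adherence and missing data, {20c}.** Marked not applicable, and then: "Non-compliance with the protocol and missing data, we plan not to use as part of the statistical analysis".
- **PPS, {19}.** Requires "receiving treatment, availability of the primary endpoint measures, and no major trial protocol violations". "The per-protocol analysis is used mainly for the primary efficacy measures".
- **Primary endpoint, {12}.** Effective analgesia means a resting NRS of 3 or less at every one of eight time points, from 1 min after ablation to 48 h after surgery. Use of another analgesic and stopping the study drug play no part in the definition.
- **Blinding, {17a}.** Only patients are blinded.

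**The concern.** Sections {19} and {20a} keep a disenrolled patient in the primary analysis. Section {20c} takes the patient's data out. Both cannot hold, and each leaves a weakness.

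- **If {20c} governs,** patients leave the numerator and the denominator for reasons linked to pain control and tolerability. Staff who know the allocation judge whether a prohibited drug prevented evaluation, and whether to invite a withdrawal.
- **If {19} governs,** the patient stays in. Anyone who had no resting NRS of 4 or more recorded before stopping, or before taking another analgesic, can then be scored a success, either by carrying a low score forward or through low scores that the other drug produced.

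The PPS would normally be the cross-check in a non-inferiority comparison. Here it drops most of the same patients, for a missing endpoint or a major violation, so agreement between the two sets would not be reassuring. What is at stake is the primary test against the 10-point margin.

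**Working it through.** **1. The plan's own figure.** Sample size {14} assumes 90% v 90%, a margin of 10 points, one-sided alpha 0.025 and power 0.8. n per arm = (1.960 + 0.842)² × (0.9×0.1 + 0.9×0.1) / 0.10² = 141.3, so 142 per arm and 284 in all; 284 / 0.9 = 315.6, so 316. This reproduces. The dropout allowance (316 − 284 = 32 patients) is about as large as the number of failures expected (10% of 284 = 28.4), so the affected group need not be small beside the failures that drive the result.

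**2. One patient under each rule.** Take a patient with resting NRS of 3 or less at every scheduled reading up to 2 h, pain between readings, another analgesic given, then disenrolment.

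| Rule | Result |
|---|---|
| {19}/{20a}, with last observation carried forward | In the FAS, scored effective |
| {20c} | Not used |
| PPS in {19} | Excluded if the endpoint is unavailable or the violation is major |
| Same patient, but one scheduled resting NRS of 4 or more | In the FAS under {19}: not effective, permanently, by the {12} definition |

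**3. Size if failures are removed, as under {20c}.** Assumptions, none from the documents: true rates at the margin, nalbuphine 80% and morphine 90%; 150 analysed per arm; a share d of each arm removed, all failures. Observed rate = p / (1 − d). The decision rule is the article's: lower 95% limit of the difference above −10 points, here with a Wald interval and exact enumeration of the two binomials.

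| Removed, nalbuphine / morphine (points) | Observed rates | Difference (points) | False non-inferiority |
|---|---|---|---|
| 0 / 0 | 80.0% / 90.0% | −10.0 | 2.7% |
| 2 / 1 (10% of failures) | 81.6% / 90.9% | −9.3 | 4.1% |
| 5 / 2.5 (25% of failures) | 84.2% / 92.3% | −8.1 | 7.9% |
| 10 / 5 (50% of failures) | 88.9% / 94.7% | −5.8 | 27.8% |
| 5 / 5 | 84.2% / 94.7% | −10.5 | 2.1% |
| 2.5 / 5 | 82.1% / 94.7% | −12.7 | 0.4% |

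For example, 0.80 / 0.95 = 0.842 and 0.90 / 0.975 = 0.923. With 142 per arm the 25% and 50% rows become 8.2% and 26.9%.

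**4. Size if failures are scored as successes, as can happen under {19}.** Same true rates, 158 per arm (316 / 2). If a fraction f of each arm's failures is so scored, the rates become 0.80 + 0.20f and 0.90 + 0.10f. For f = 10%, 25% and 50%, false non-inferiority is 4.8%, 11.3% and 41.1%.

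**5. Does the scoring rule alone move the result?** Take 158 per arm, 90% success among those retained, and assume 10% (nalbuphine) and 5% (morphine) disenrolled. P(non-inferiority) = Φ[(0.10 + difference) / SE − 1.96].

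- Excluded: 90% v 90%, probability 0.81.
- All counted as failures: 0.9×0.90 = 81.0% v 0.9×0.95 = 85.5%, difference −4.5 points, probability 0.26.
- With 5% disenrolled in both arms, the two figures are 0.82 and 0.71.

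**The case against.** A reader might infer that these patients, the clearest treatment failures, leave both the FAS and the PPS. The documents do not support that.

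- The FAS definition in {19}, repeated in {20a}, has no exclusion for disenrolment or prohibited drugs. The first reading comes at 1 min, so nearly all such patients qualify. Removal from the FAS rests on one poorly worded sentence in {20c}, which might mean only that no special method is planned.
- Section {11b} lists grounds for disenrolment and does not say that data are discarded. Its third ground covers only drugs that prevented evaluation, not any other analgesic.
- Under the FAS definition a patient with one recorded resting NRS of 4 or more is already a permanent failure, and neither a later analgesic nor a carried-forward score reverses that. The group at risk is narrower: pain between readings, or a stop with good scores so far.

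A reader might also infer that the bias always favours non-inferiority. It does not. The 8% and 28% results take twice as many points from nalbuphine as from morphine. Equal removal gives 2.1%, and heavier removal on morphine gives 0.4%. The background section expects fewer side effects with nalbuphine, so more adverse-event removals on morphine are plausible.

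Finally, stopping for nausea with an NRS of 3 or less is not an analgesic failure, and adverse reactions are assessed in their own right. Scoring such stops as failures is an estimand choice.

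All of this stands and limits the point. It could be added that such rules are often left to an analysis plan. That does not answer the contradiction, because the article states both rules itself.

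**Conclusion.** The point holds as a contradiction with consequences for the primary result. Sections {19} and {20a} cannot be reconciled with {20c} as written, and {12} does not say how another analgesic or a stop is scored when recorded scores stay at 3 or below. The PPS shares most of the same exclusions and cannot settle the matter.

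Size and direction are conditional. If true rates sit at the margin, false non-inferiority ranges from 0.4% to 28% across the removal splits shown, against a nominal 2.5% (2.7% for this interval with no removal). It reaches 41% if half of all failures were scored as successes at 158 per arm, an extreme case because recorded scores of 4 or more already count as failures. The removed or rescored shares are assumptions. The documents give only the margin, the rates for planning and the 10% dropout allowance. The sample size itself is correct.

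**What to change.** 1. Reconcile {11b}, {19}, {20a} and {20c}: delete the {20c} statement and keep the FAS definition.
2. Separate stopping the study drug from leaving the study, and keep recording NRS and adverse reactions to 48 h for every treated patient.
3. In the FAS, replace carrying forward for these patients by a scoring rule: another analgesic taken for pain, or stopping for lack of effect, within 48 h counts as not effective.
4. Analyse adverse-event stops on their observed NRS, with a sensitivity analysis that scores them as not effective.
5. Report by arm how many patients the PPS excludes for analgesic use, and add a PPS sensitivity analysis that keeps them as not effective.

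These changes concern data collection and scoring only; no change to the care given is proposed. The cost is wording in the protocol and analysis plan and a few more readings. The stated effective rate may fall slightly. The change to data collection is the urgent one, because readings not taken after disenrolment cannot be recovered.

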### Strategies to improve adherence to interventions {11c}

To improve subject compliance, open recruitment was used, and patients were screened according to the inclusion and exclusion criteria of the study; informed consent should follow the Standard Operating Procedures for Signing Informed Consent, and after the investigator fully informed the subjects about the trial, the subjects’ right to decide whether or not to participate in the trial was respected either voluntarily or after discussion with their families; follow-up visits were arranged for the subjects during the trial, and all examinations were completed in strict accordance with the protocol.

### Relevant concomitant care permitted or prohibited during the trial {11d}

During the study period,in addition to the test drug, other analgesic drugs (such as non-steroidal analgesics, antidepressants, etc.) shall not be newly added during the test period, but other drugs that do not affect the efficacy of opioids can be used.

### Provisions for post-trial care {30}

The investigator will make every effort to prevent and treat any harm that may result from this study. If any damage related to the study occurs in the study, the treatment cost and corresponding economic compensation will be provided in accordance with the provisions of The Quality Management Standard for Drug Clinical Trials in China.

### Outcomes {12}

#### Main study outcome

Analgesic effective rate: Analgesic effective rate = number of patients with effective analgesia/total number of cases × 100%. NRS score (at rest) ≤ 3 points at all assessment time points is considered as effective analgesia and assessed at 1 min and 5 min after ablation, at the end of the surgery, and at 2 h, 6 h, 12 h, 24 h, and 48 h after surgery. The NRS is used for assessment, which consists of 11 numbers with the same interval from 0 to 10, with 0 representing “no pain” and 10 representing “most intense pain.” Patients are asked to choose one number to represent the pain intensity score.

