#### Statistical analysis method

The number of included and completed cases in the overall and each site is listed in the case analysis, and three analysis datasets (FAS, PPS, and SS) are generated. Dropouts and excluded cases along with the reasons for their dropping out and exclusion are listed.Demographic and baseline data analysis: Descriptive statistics of demographic data and other baseline characteristic values: For continuous variables, total number of cases, mean, standard deviation, median, and minimum and maximum values are calculated. The t-test will be used for normally-distributed data and the rank-sum test will be used for data with skewed distribution. Frequency and proportion are calculated for countable and grade data. The chi-square test will be used for disordered classification data, and the rank-sum test will be used for ordinal data. Inferential statistical results (*P*-values) are presented based on descriptive statistics.Efficacy analysis:A.Analysis of the primary efficacy indicators (overall response rate): The overall response rate is compared using the chi-square test, corrected chi-square test, or exact probability test. The 95% confidence interval of the difference in response rates between the two groups will be calculated, and if the lower limit of the confidence interval is greater than −10%, the result will be considered non-inferior.B.Analysis of the secondary efficacy indicators: Differences in the scores of NRS at each time point and the total score between the two groups are compared by the *t*-test or rank-sum test; differences in the physician satisfaction VAS score and the nurse satisfaction VAS score between the groups are compared by the t-test or rank-sum test; the difference between the two groups regarding willingness to undergo ablation surgery another time will be compared by the chi-square test, corrected chi-square test, or exact probability test; differences between the two groups with respect to duration of surgery, postoperative hospital stay, and average daily dose will be compared by the t-test or rank-sum test; the difference in the uninterrupted completion rate of surgery without complaints of pain between the groups will be compared by the chi-square test, corrected chi-square test, or exact probability test.Safety analysis: The incidence of adverse reactions will be calculated, their frequency and proportion were systematically listed, and the percentage calculated. A detailed list of cases of various adverse events (AEs), the number and rate of cases, conversion of physical examination indicators, ECG, respiratory and circulatory indicators, and laboratory indicators that “turn normal to abnormal” or “intensify abnormal” after the test, and list clinical explanations will be recorded.

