## Statistical methods

### Statistical methods for primary and secondary outcomes {20a}

All subjects who were randomized, received the trial drug, and had data on at least one post-dose efficacy evaluation were included in the outcome analysis. The number of different organ tumors, single or multiple tumor tissues, and different ablation techniques were compared between the two groups to determine whether they were comparable.

Statistical analyses are performed using the SAS 9.4 software. Unless otherwise specified, the level of statistical significance was set at *P* ≤ 0.05. For a non-inferiority test, a one-sided test will be used, and *P* ≤ 0.025 are considered statistically significant.

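### Scored by NRS alone with LOCF, a patient given a barred analgesic for pain between readings can count as effective in the FAS or be dropped from the PPS; if commoner on nalbuphine, this favours non-inferiority

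*Protocol article*

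**What the plan says.** All references are to the protocol article.

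- **Endpoint.** Main study outcome under Outcomes {12}: a resting NRS of 3 or less "points at all assessment time points is considered as effective analgesia". There are eight readings: 1 and 5 min after ablation, end of surgery, then 2, 6, 12, 24 and 48 h. Section {18a} also defines success by NRS alone at scheduled readings. Use of another analgesic is not part of either definition.
- **Extra analgesics.** Section {11d}: other analgesics "shall not be newly added during the test period". No consequence for the endpoint is attached.
- **Disenrolment.** Section {11b}, third criterion: "combination of prohibited drugs during the study period that prevented satisfaction and effectiveness evaluation".
- **FAS and missing data.** Section {20a} analyses randomized, treated patients who "had data on at least one post-dose efficacy evaluation were included in the outcome analysis". Section {19} says that for missing primary data "the last observation carried forward is applied according to the intention-to-treat principle".
- **PPS.** Section {19} requires "availability of the primary endpoint measures, and no major trial protocol violations".
- **A competing rule.** Section {20c}: "Non-compliance with the protocol and missing data, we plan not to use as part of the statistical analysis".
- **Decision.** Statistical analysis method: if the lower 95% limit for the difference in rates is above −10%, "the result will be considered non-inferior".

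**The concern.** A patient who needed a different analgesic for procedural pain was not controlled by the study drug. The stated rules do not record that as a failure unless a scheduled score above 3 was also obtained.

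Take a patient with scores of 3 or less through 6 h who is given a barred analgesic for pain at 9 h.

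- **Disenrolled, FAS.** LOCF fills the 12, 24 and 48 h readings from the 6 h score, and the patient is effective.
- **Kept in the trial, FAS.** The 12 h score is taken under the other drug. If it is 3 or less, and the later ones are too, the patient is effective.
- **PPS.** The patient can be excluded as a major violator, or for lacking primary readings.
- **Section {20c} read literally.** The patient may be left out, which is not a failure either.

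In a non-inferiority comparison the PPS usually serves as a check on the FAS. Here both sets treat the same patient leniently, so agreement between them would not be reassuring on this point.

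**Working it through.** **1. The plan's own figure.** Inputs from Sample size {14}: 90% versus 90%, margin 10%, one-sided α 0.025, power 0.80, dropout 10%.

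n per arm = (1.960 + 0.842)² × 2 × 0.90 × 0.10 / 0.10² = 141.3, rounded up to 142. Total 284; 284 / 0.9 = 316. The stated 142, 284 and 316 reproduce. The sample-size arithmetic is not at fault.

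**2. Break-even.** Unpooled limit: d − 1.960 × √[p₁(1−p₁)/142 + p₂(1−p₂)/142], with morphine fixed at 128/142 (90.1%).

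| Nalbuphine effective | Difference | Lower limit | Rule |
|---|---|---|---|
| 121 (85.2%) | −4.9% | −12.6% | fail |
| 124 | −2.8% | −10.2% | fail |
| 125 | −2.1% | −9.4% | pass |

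From 121 true successes, a net 4 of 142 (2.8%) miscounted as effective turns a fail into a pass. From 114 (80.3%) it takes 11 (7.7%).

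**3. Chance of a false pass.** Exact binomial, 142 per arm, assumed true rates 80% nalbuphine and 90% morphine (exactly at the margin). Recorded rate = true rate + share miscounted as effective. The shares are assumptions, because the protocol article gives none.

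| Miscounted, nalbuphine | Miscounted, morphine | Chance of declaring non-inferiority |
|---|---|---|
| 0% | 0% | 2.8% |
| 1% | 0% | 4.7% |
| 2% | 0% | 7.7% |
| 3% | 0% | 12.1% |
| 5% | 0% | 26.0% |
| 3% | 2% | 5.1% |
| 3% | 3% | 3.0% |
| 2% | 3% | 1.6% |

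Only an excess on nalbuphine inflates the error.

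**4. The PPS.** Constructed example, 142 per arm: 126 versus 128 effective by NRS, of whom 7 versus 2 had a barred analgesic for pain.

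- NRS only, 126/142 v 128/142: lower limit −8.6%, pass.
- Counted as failures, 119/142 v 126/142: −12.9%, fail.
- Dropped, 119/135 v 126/140: −9.2%, pass.

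In this example dropping the patients gives the same verdict as counting them effective.

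**5. Power once such patients fail.** Exact, equal true rates in both arms.

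| Common rate | 142 per arm | 158 per arm (all 316 in the FAS) |
|---|---|---|
| 90% | 81% | 84% |
| 88% | 74% | 78% |
| 85% | 66% | 70% |

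By the formula in step 1, 80% power needs 166 per arm at 88% and 201 at 85%.

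**The case against.** **This is detail for an SAP or the full protocol.** Partly fair: each rule is conventional on its own. But the article itself fixes the endpoint, disenrolment, LOCF and PPS rules, and followed as written they can turn a treatment failure into a success.

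**The path is narrow.** This stands. The pump allows a 2 ml bolus at NRS 4 or more with a 15-min lockout, so up to four an hour, and five of the eight readings fall by 6 h. A miscount needs pain between readings, boluses that do not suffice, a breach of section {11d}, and no scheduled score above 3. A bolus is study drug and is not part of this point.

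**Sample size {14} counts the whole 48 h.** Its wording could be read to make an unscheduled score of 4 or more a failure. But it too is NRS-only, and the outcome sections tie success to assessment times.

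**If section {20c} governs, LOCF is not applied.** True. The patient would then be left out rather than failed, so the miscount changes form. The conflict between {19} and {20c} is a separate defect and adds no weight to the size of this one.

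**The direction is unknown.** This stands. A reader might infer that the plan is biased towards nalbuphine. Nothing in the protocol article shows that barred analgesics will be used more in that arm, and the 12.1% and 26.0% figures need a net excess of 3 or 5 points there.

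**Disenrolments will be visible.** Dropouts and exclusions are to be listed with reasons. That helps detection, but does not change how the patient is scored.

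**Conclusion.** The point holds in limited form. As written, a patient given a newly added analgesic for procedure-related pain, with no scheduled score above 3, can be effective in the FAS or absent from the PPS. If such use is commoner on nalbuphine, both sets lean towards non-inferiority. If it is equal, the effect is negligible (3.0% against 2.8%). If it is commoner on morphine, the bias runs against nalbuphine.

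The size is unknown. The figures above are break-evens and assumed scenarios, resting on 142 per arm, an unpooled 95% interval and assumed shares. Two stronger readings are not supported. One is that every patient who takes a barred analgesic escapes failure: a recorded scheduled score above 3 still fails the patient. The other is that the trial's conclusion will be wrong: no rate or direction of use is given. Correction is still worthwhile, because a net handful of patients can decide a result near the margin and the change is small.

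**What to change.** 1. In Data management {19}, state that LOCF does not apply to readings missing after a newly added analgesic, barred under {11d}, given for procedure-related pain within 48 h. Such a patient stays in the FAS as not effective, whatever the later scores, and is not excluded from the PPS for that reason alone.
2. State that permitted continuing analgesics and drugs for unrelated pain do not count. Section {11d} bars only new additions, so a broader rule would fail patients who kept to the protocol.
3. Delete the sentence in {20c} or align it with {19}.
4. Record drug, time and reason on the case report form.
5. Report the NRS-only result as a sensitivity analysis. Only patients are blinded {17a}, so staff who give or withhold the drug know the arm, and the new rule brings their decision into the endpoint.

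**Cost.** An amendment with ethics approval while enrolment is under way, and one form entry. Section {18b} has patients report their own drug use, so for those already treated, staff-given analgesics would have to come from hospital records. The effective rate may fall, with the loss of power shown in step 5. Power should be restated under the new rule.
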